van der Vliet et al [19] advises additional research in nontechnical skills to be performed in different surgical approaches (open, laparoscopic, and robot assisted). Moreover, the use of multiple trained observers is advised for assessing audiovisual recordings of the surgical environment to identify and quantify possible interobserver reliability. The group of Gjeraa et al [18] advises systematic identification of nontechnical skills in minimally invasive surgery in order to develop effective, evidence-based team training programmes for minimally invasive surgeries.

The present study aims to perform a structured evaluation of nontechnical skills in both open and robot-assisted complex surgery, to investigate the manner in which the introduction of a surgical robot influences both nontechnical skills and surgical outcomes during the 1st year of robot-assisted radical cystectomy compared with open radical cystectomy.

In addition, analysis of technical skills in robot-assisted radical cystectomy will be performed to evaluate the possible relationship between technical and nontechnical skills. Radical cystectomy was chosen for this analysis because it is a lengthy, complex, and demanding surgery for the surgeon and other team members.

Since radical cystectomy surgeries take many hours to complete, a long-term and detailed analysis is possible per procedure. Radical cystectomy is traditionally performed using an open surgical approach (open radical cystectomy) at the Catharina Hospital Eindhoven, but recently a shift is made to robot-assisted radical cystectomy. This shift enables us to investigate in which manner nontechnical skills change during the introduction of robot-assisted radical cystectomy. The nontechnical skills during the learning curve of robot-assisted radical cystectomy in the Catharina Hospital Eindhoven will be compared with the nontechnical skills during the open radical cystectomy in the same hospital as well the nontechnical skills of an experienced robot-assisted radical cystectomy team in the Antoni van Leeuwenhoek Hospital.

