These analyses will be performed in order to investigate in which manner nontechnical skills change during the introduction of the robot-assisted radical cystectomy and which factors contribute to the learning curve. Results obtained during this study could be beyond robot-assisted radical cystectomy, since the changes in operating OR set-up and the loss of nonverbal communication are universal when making the shift from open to robot-assisted surgery.

Our hypothesis includes the following:1.Introduction of robot-assisted surgery leads to an initial decay in nontechnical skills behaviour during the learning curve of the team.2.In experienced robot-assisted surgery teams, nontechnical skills behaviour is more explicitly expressed than in experienced open surgery teams.3.Introduction of robot-assisted surgery leads to the development of different forms of nontechnical skills behaviour compared with open surgery.

The results of this study could possibly be used to develop team training programmes specifically for the introduction of the surgical robot in relation to changes in nontechnical skills. Additional analysis of technical skills using the intracorporeal footage of the surgical robot will be used to elucidate the role of surgical skills and surgical events in nontechnical skills.

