## Statistical analysis

Frequency statistics will be calculated for patient demographical data, and a Shapiro-Wilk test with *p* > 0.05 will be used to define normal distribution. Univariate analysis will be conducted to test for statistically significant differences in observation scores between open radical cystectomy and robot-assisted radical cystectomy cohorts across all variables, using independent sample *t* tests and Mann-Whitney *U* testing, as appropriate. A variable-selection strategy will be used to create multivariate models. Binary logistic regression will be conducted to calculate odds ratios and 95% confidence intervals for significant predictors on univariate analysis and clinically relevant covariates. Statistical significance is set at *p* < 0.05 based on a two-tailed comparison. Statistical analyses will be performed using SPSS Statistics version 24 (IBM, Armonk, New York, USA).

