### Privacy

Observations during surgery will be performed by two members of the urology in-house staff (medically trained researchers with training in the analysis of both nontechnical and technical skills); none of the observers have a hierarchical relationship with any of the team members.

As discussion of planned surgeries is part of daily staff meetings, there are no additional privacy concerns.

The observations do not contain the name of the patient, or the date and time of surgery. This is in accordance with the General Data Protection Regulation.

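### The statistical section specifies only an open versus robot-assisted test by technique; it omits the comparisons announced in the Introduction and does not match hypotheses 1 and 2

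*Protocol article*

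**What the plan says.** Under Introduction and hypotheses, the Protocol article states H1 as "Introduction of robot-assisted surgery leads to an initial decay in nontechnical skills behaviour during the learning curve of the team" and H2 as "In experienced robot-assisted surgery teams, nontechnical skills behaviour is more explicitly expressed than in experienced open surgery teams". H3 expects different forms of behaviour under robot-assisted than under open surgery.

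The same section announces two comparisons for nontechnical skills in the learning-curve robot cases at the Catharina Hospital (Eindhoven). It says that these "will be compared with the nontechnical skills during the open radical cystectomy in the same hospital as well the nontechnical skills of an experienced"; the sentence goes on to name the Antoni van Leeuwenhoek Hospital (Amsterdam) as the place of that second, robot team.

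The Statistical analysis section, repeated in the Abstract, tests "differences in observation scores between open radical cystectomy and robot-assisted radical cystectomy cohorts across all variables". The method is given as "using independent sample *t* tests and Mann-Whitney *U* testing, as appropriate". It adds: "Statistical significance is set at *p* < 0.05 based on a two-tailed comparison". Multivariable models follow by variable selection, with covariates that are not named. Hospital, team experience and case number do not appear in the section.

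**The concern.** H1 and H2 are both conditional on team experience, and they point in opposite directions. A two-group test by technique puts the learning robot team and the experienced robot team into one group. If hospitals are pooled, it estimates an average of two effects that the study expects to differ in sign. It also cannot express an initial decay, which is a statement about the order of cases.

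The stake is the study's stated use, which is team training for the introduction of the robot. A real decay in Eindhoven could be reported as no difference, or as a gain that comes from the larger Amsterdam volume.

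**Working it through.** **1. Hypotheses against stated comparisons**

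| Hypothesis | Contrast it needs | Introduction | Statistical analysis |
|---|---|---|---|
| H1 | Eindhoven robot vs Eindhoven open, with case order | Comparison announced; no case-order term | Neither |
| H1, supporting | Eindhoven robot vs Amsterdam robot | Announced | Not stated |
| H2 | Experienced robot vs experienced open | Hypothesis only | Not stated |
| H3 | Robot vs open | Hypothesis only | Fits the stated test |

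**2. Expected case mix.** The plan gives no sample size or effect size, so there is no figure to reproduce. Inputs:
- Centre details: Eindhoven has 35 cystectomies a year, half of them expected to be robot-assisted; Amsterdam has 50 robot and 50 open a year.
- Time scales: inclusion runs from January 2021 to August 2022, which is 20 months.

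Results:
- Eindhoven: 35/2 = 17.5 per technique per year; 17.5 × 20/12 = 29.2.
- Amsterdam: 50 × 20/12 = 83.3 per technique.
- Pooled: 112.5 per technique.
- Learning-team share of robot cases: w = 17.5/67.5 = 0.26, whatever the common inclusion period.

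**3. What a pooled test estimates.** Let d1 and d2 be the robot-minus-open differences in Eindhoven and Amsterdam, in SD units. With equal open means in the two hospitals:

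pooled difference = w·d1 + (1 − w)·d2 = 0.26·d1 + 0.74·d2

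The expected hospital mix is the same in both cohorts, so the formula also holds for unequal open means as long as that balance is realised. The effects below are assumptions.

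| d1 | d2 | Pooled |
|---|---|---|
| −0.5 | +0.5 | +0.24 |
| −0.5 | +0.2 | +0.02 |
| −0.5 | 0 | −0.13 |
| −0.8 | +0.3 | +0.02 |

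Equal and opposite effects leave 0.74 − 0.26 = 48% of the gain, with the sign of H2. Full cancellation needs |d1|/d2 = 50/17.5 = 2.9, for example 0.86 against 0.30 SD.

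**4. Power at 20 months.** Normal approximation, two-sided 0.05, rejections in the direction of the effect only. The pooled SD allows for the mixture of two robot teams. Full recruitment is assumed.

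| d1, d2 | Pooled (about 112 per group) | H1 in Eindhoven (about 29 per group) | H2 in Amsterdam (about 83 per group) |
|---|---|---|---|
| −0.5, +0.5 | 41% | 48% | 90% |
| −0.8, +0.3 | 3% | 86% | 49% |

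In these two scenarios the larger pooled groups give less power than either separate contrast.

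**5. Whether the multivariable models help.** Adding hospital as a main effect leaves one common technique effect, which is still a weighted average of d1 and d2. Only an interaction of technique with hospital, or separate contrasts, keeps them apart.

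**The case against.** The best defence is that the Introduction does plan comparisons by hospital, and that the t and Mann-Whitney tests are simply the method for them. The word cohorts does not say that hospitals are combined, and a condensed article may leave contrasts to a fuller plan. This stands in part: pooling is an inference. But the article does state its comparison, and what it states is by technique alone. It differs from the Introduction, and neither place supplies the contrast for H2.

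Four stronger readings are tempting, and the documents do not support them:

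- A reader might infer that no other comparison is planned. The Introduction announces two, and the within-Eindhoven one addresses H1.
- A reader might infer that the pooled test answers no hypothesis. It fits H3.
- A reader might infer that case order is lost, because "The observations do not contain the name of the patient, or the date and time of surgery" and the code lists are destroyed. That sentence concerns the observations, and Data collection and handling destroys the lists only after video results and patient characteristics are matched. Order can be carried over at that step, and the surgeon's prior robot experience is recorded. What is true is that no section requires case order to be kept.
- A reader might set the 20-month inclusion against the aim of studying "surgical outcomes during the 1st year of robot-assisted radical cystectomy compared with open radical cystectomy" and compute a share of cases beyond the first year. The start date of the Eindhoven robot programme is not given, so no share follows.

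It is also fair to say that the effect sizes are illustrative. More explicit expression in H2 might further mean frequency or duration of labelled behaviour rather than a higher score, in which case opposite signs on one scale are not certain.

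**Conclusion.** The mismatch is real. The statistical section omits the comparisons announced in the Introduction, has no case-order term for H1, and leaves H2 without a stated contrast anywhere.

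If the test is run pooled, the learning team carries about 26% of the weight. That weight follows from the plan's own volumes; the resulting effects and power rest on assumed effect sizes, full recruitment, the even split in Eindhoven, and equal open means or a balanced hospital mix. Cancellation is usually partial, since it is complete only near a ratio of 2.9. Masking of H1 needs much less: with equal and opposite effects of 0.5 SD the pooled estimate is +0.24 SD, the wrong sign for H1.

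This should be corrected before analysis, because it decides what the study can conclude on two of its three hypotheses.

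**What to change.** In the Statistical analysis section, replace the pooled test for H1 and H2 with a technique-by-hospital model that includes the interaction, or with separate contrasts:

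- **H1:** Eindhoven robot against Eindhoven open, with the trend in score over robot case number within Eindhoven. Eindhoven robot against Amsterdam robot is supporting.
- **H2:** Amsterdam robot against Amsterdam open. The article calls only the Amsterdam robot team experienced; treating its open team as experienced rests on the 50 open cases a year and should be stated.
- **H3:** the open against robot comparison may stay, labelled as such.

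Keep a non-identifying robot case sequence number in the coded dataset, added before the code lists are destroyed.

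The cost is analysis wording, one coded variable and smaller cells: about 29 against 29 in Eindhoven, with about 48% power for an assumed 0.5 SD.

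The plan should also state a limit that no model removes. Under Study population, one surgeon does all open cases and another all robot cases in Eindhoven, so technique there is confounded with surgeon. In Amsterdam one surgeon does both.

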### Data collection and handling

Data collection will consist of video capturing and analysis of patient records. Two trained observers (observer 1 and 2, both have a background in medicine), with orientation and training in both nontechnical skills and technical assessment methods, will independently observe surgical videos. All videos will be analysed by both researchers. In case of disagreement, a third independent expert with a psychology and leadership assessment background (observer 3) will be asked to perform a third analysis. Inter-rater reliability will be analysed using Cohen's kappa.

The surgical video will be assessed in multiple phases; in each phase, a nontechnical skills assessment method will be used to assess nontechnical skills. Surgical videos will be analysed using customisable video analysis software “Digital Video Coach” developed by ZEAL IT, Einhoven, The Netherlands (Fig. 2).

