### Primary outcome measurements

The following outcomes will be reported.

Nontechnical skills will be observed using five different methods:1.NOTSS [16]: The focus of the NOTSS assessment method lies on the following aspects of nontechnical skills:(a)Situation awareness: developing and maintaining dynamic awareness of the situation in operating theatre based on assembling of data from the environment, understanding of what they mean, and thinking ahead about what may happen next.(b)Decision making: skills for diagnosing the situation and reaching a conclusion in order to choose an appropriate course of action.(c)Communication and teamwork: skills for working in a team context to ensure that the team has an acceptable shared overview of the situation and can complete tasks effectively.(d)Leadership: leading the team and providing direction, demonstrating high standards of clinical practice and care, and being considerate about the needs of individual team members.2.Oxford NOTECHS II [11], [12]: The focus of the NOTECHS II assessment method lies on the following aspects of nontechnical skills:(a)Leadership and management.(b)Teamwork and cooperation.(c)Problem solving and decision making.(d)Situation awareness.3.OTAS [21]: ^The^
^focus^
^of^
^the^
^OTAS^
^assessment^
^method^
^lies^
^on^
^the^
^following^
^aspects^
^of^
^nontechnical^
^skills:^(a)Communication.(b)Coordination.(c)Cooperation and back-up behaviour.(d)Leadership.(e)Team monitoring and situational awareness.4.ICARS [17]: The focus of the ICARS assessment method lies on the following aspects of nontechnical skills:(a)Checklist and equipment.(b)Interpersonal skills (communication and team skills, and leadership).(c)Cognitive skills (decision making and situational awareness).(d)Resource skills (stress and distractors).(e)Human factor analysis [22]: Human factor analysis consists of four levels of system failure: unsafe acts, preconditions for unsafe acts, unsafe supervision, and organisational influences.5.Perioperative events (ie, people entering or leaving the OR, phone calls, etc.).

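### Predictors for the logistic models are chosen by univariate significance on the same data, with nothing stated to keep overlapping ratings of one skill out of the same model

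*Protocol article*

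**What the plan says.** The Statistical analysis section of the Protocol article describes three steps.

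- **Screen.** "Univariate analysis will be conducted to test for statistically significant differences in observation scores between open radical cystectomy and robot-assisted radical cystectomy cohorts across all" the recorded items, by t test or Mann-Whitney U, at p < 0.05 "based on a two-tailed comparison".
- **Model building.** "A variable-selection strategy will be used to create multivariate models". The strategy is not named, and the models are plural.
- **Reporting.** "Binary logistic regression will be conducted to calculate odds ratios and 95% confidence intervals for significant predictors on univariate analysis and clinically relevant covariates". The binary dependent variable is not named.

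The candidate scores come from Primary outcome measurements: "Nontechnical skills will be observed using five different methods". Four of these are rating instruments with similar domain lists. Situation awareness, for example, is a domain of NOTSS and of NOTECHS II. It appears in OTAS as "Team monitoring and situational awareness" and in ICARS within "Cognitive skills (decision making and situational awareness").

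Under Data collection and handling, the same two observers rate all videos, and "in each phase, a nontechnical skills assessment method will be used to assess nontechnical skills".

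**The concern.** Ratings of one skill by several instruments, made by the same observers on the same recording, can be expected to correlate. If the skill differs on the screened comparison, its several versions tend to pass the screen together. The stated rule then makes all of them eligible for the logistic models.

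Two things can follow.

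- **Joint entry.** Each Wald test and interval asks whether one instrument adds anything once near-duplicate ratings are held fixed. None of the three hypotheses in the Introduction asks that.
- **Pruning by selection.** One instrument survives among several that measure the skill about equally well. Its ordinary p value and confidence interval take no account of the screening and selection done on the same data.

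At stake is whether the adjusted odds ratios can be read as evidence about a skill, or about the merits of an instrument.

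**Working it through.** **The plan's own figure.** There is none to reproduce: the article gives no between-scale correlation, event share or effect size for these models.

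**Overlap, from Primary outcome measurements**

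| Skill | NOTSS | NOTECHS II | OTAS | ICARS |
|---|---|---|---|---|
| Leadership | yes | yes | yes | yes |
| Situation awareness | yes | yes | yes | yes |
| Communication, teamwork or cooperation | yes | yes | yes | yes |
| Decision making | yes | yes | no | yes |

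**Upper bound on N.** Time scales gives January 2021 to August 2022, about 20 months. Centre details gives 35 and 50 + 50 = 100 cystectomies a year.

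- Catharina: 35 × 20/12 ≈ 58.
- Antoni van Leeuwenhoek: 100 × 20/12 ≈ 167.
- Together: 135 × 20/12 = 225, if every operation is included.

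**Variance inflation.** For k scales with common correlation ρ, R² = (k − 1)ρ² / (1 + (k − 2)ρ) and VIF = 1/(1 − R²).

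- k = 3, ρ = 0.6: R² = 0.72/1.6 = 0.45, VIF = 1.82, standard error × 1.35.
- k = 3, ρ = 0.8: R² = 1.28/1.8 = 0.711, VIF = 3.46, standard error × 1.86.
- k = 4: VIF = 1.60 at ρ = 0.5, 2.58 at 0.7 and 7.57 at 0.9.

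Inflation is only part of the loss. The shared effect is also divided among the scales, so each coefficient shrinks.

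**Simulation with three scales.** These are assumptions, not figures from the article: one latent skill, three ratings with pairwise correlation 0.6-0.8, a binary dependent variable with about 30% events, and four covariates. Ratings with t test p < 0.05 enter the model. The last column applies backward elimination, as one ordinary selection strategy.

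| Setting | One prespecified scale | Joint entry: a given scale | Joint entry: any of three | Backward elimination keeps at least one |
|---|---|---|---|---|
| N = 225, OR 1.6 per SD | 69-77% | 8-16% | 27-41% | 85-89% |
| N = 225, OR 2.0 per SD | 94-98% | 13-22% | about 41-61% | 99% or more |
| N = 58, OR 2.0 per SD | about 37-50% | 7-12% | not tabulated | 59-62% |
| No effect | about 5% | about 2% | 5-7% | about 8-9% |

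Even counting any of the three scales as success, joint entry loses 68.9 − 41.3 = 27.6 points (N = 225, ρ = 0.6, OR 1.6) to 97.9 − 40.5 = 57.4 points (N = 225, ρ = 0.8, OR 2.0). In N = 225 runs with a true effect where all three scales entered, signs conflicted in roughly 30-63%.

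**Separate check with four scales** (ρ 0.5-0.9, outcome share 20% or 50%).

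- N = 225, OR 2.0: each scale alone is significant in 82-99.7% of runs, but inside the joint model in 6-19%. When all four passed the screen, none was significant jointly in 36-77% of runs, although the joint likelihood-ratio test had 85-98% power.
- N = 58, OR 2.5: the joint per-scale rate is 5-10%.
- Backward elimination never lost every scale once all four had passed. It kept exactly one in 55-98% of those runs at N = 225 and in 82-99.7% at N = 58, although all four measured the skill equally well.

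**The case against.** The strongest reply is that the article does not prescribe joint entry. A reader might infer that every significant score goes into one model and that a real effect will therefore be hidden. The words do not support that: they speak of a selection strategy and of models in the plural, so separate models or removal of redundant scales would fit. The simulations bear this out, since the large power loss appears only under joint entry. A full analysis plan may also name the strategy, and leaving that name out of an article is no fault. This stands. What it does not remove is the rule that the article does fix: entry by univariate significance on the same data.

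Other points also limit the claim.

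- **The univariate results remain visible.** A score that enters has already shown an association on its own. The damage is to the adjusted odds ratios.
- **The simulated screen is not exactly the written one.** The article screens scores between open and robot-assisted cohorts. If surgical approach is the dependent variable, the split is near 50:50 and the odds ratios describe discrimination between approaches. If it is a clinical outcome, the screen was on something else, and overlapping scores need not pass it together because they predict that outcome.
- **Shared labels may overstate overlap.** The Introduction separates whole-team tools from tools for individual members. ICARS is a robotic tool and may not be available for open cases. The three-scale simulation does not depend on it.
- **Correlations are assumed.** At ρ = 0.5 with four scales the VIF is only 1.6, although the joint per-scale rate at N = 225 was still at most 19%.

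**Conclusion.** The point holds in conditional form. The plan screens predictors by univariate significance on the same data, its instruments overlap by their own domain lists, and nothing stated keeps ratings of one domain apart. Either way of applying the rule does harm, of different kinds and sizes.

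- **If overlapping scores enter together,** the adjusted odds ratios are close to uninformative about the skill, and the loss of about 28 to 57 points applies.
- **If selection prunes them,** power is largely kept. What remains is a near-arbitrary choice of instrument, and about 8-9% null rejections for at least one of three scales against about 5% for one prespecified scale.

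The documents do not support saying that a true effect will be masked, because they do not fix joint entry. Nor is gross false-positive inflation shown: under joint entry the null rate for any scale is 5-7%.

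The sizes rest on assumed correlations, event shares and effect sizes, on an unnamed dependent variable taken as binary, and on N of at most about 225. The change is worth making because the stated rule is the weaker method under both readings and the alternative is cheap.

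**What to change.** In Statistical analysis, replace entry by univariate significance with the following.

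- Fit one logistic model per instrument, using its total score or one named domain, for a named dependent variable.
- Adjust for a fixed covariate set chosen in advance from the baseline items listed under Secondary outcome measurements.
- Do not put two instruments' ratings of the same domain in one model.
- Report the odds ratio and 95% confidence interval for every instrument, significant or not, and read agreement across instruments as a sensitivity check. Picking out the best-looking instrument afterwards would bring the selection problem back.

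In the four-scale check, testing each scale on its own (approximated by the univariate test) gave 82-99.7% power at N = 225 and 46-84% at N = 58.

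The cost is revised wording and a few extra models on data already being collected. The study would no longer say which instrument predicts independently of the others, but none of its hypotheses asks that.

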## Design

The present study is a prospective, observational, multicentre, nonrandomised, case-control study that will include all patients undergoing either an open radical cystectomy or a robot-assisted radical cystectomy in Catharina Hospital Eindhoven or Antoni van Leeuwenhoek Hospital.

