### Inclusion criteria

Patients who will undergo either an open radical cystectomy or a robot-assisted radical cystectomy in Catharina Hospital Eindhoven or Antoni van Leeuwenhoek Hospital are eligible for this study. The choice of treatment is at the discretion of the patient and the surgeon.

For study inclusion, the following criteria must be met:1.Patients must be aged ≥18 yr.2.Patients must be able to understand and sign an informed consent form.3.Patients will undergo either an open radical cystectomy or a robot-assisted radical cystectomy in Catharina Hospital Eindhoven or Antoni van Leeuwenhoek hospital.4.Indication for the radical cystectomy must be urothelial cell carcinoma of the bladder.5.Informed consent of the patient must be obtained to gather data and perform observations during surgery.

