### Secondary outcome measurements

Age, World Health Organization performance status, Charlson comorbidity index, neoadjuvant chemotherapy, prior local treatment, prior radiation therapy in the surgical field, diagnosis, prior abdominal and/or pelvic surgery, indication of surgery, perioperative complications, postoperative complications according to the Clavien-Dindo system [24], length of hospital stay, stay in the intensive care unit, blood loss, patient-reported experience measures, patient-reported outcome measures, method of surgery, and oncological outcome (surgical margins and number of resected lymph nodes, and pathology results) will be registered prospectively. Patient follow-up will be for at least 30 d. Surgeon-specific data will be recorded (ie, age, gender, right or left handedness, gaming experience, and prior surgical and robot-assisted surgery experience of the surgeon).

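### The published plan specifies no adjusted effect of surgical approach on the nontechnical skills scores: the tests on the scores are unadjusted, and the one regression family named, binary logistic, does not suit them

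*Protocol article*

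**What the plan says.** The Statistical analysis section of the protocol article has two parts that matter here.

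- **Comparison of approaches.** The two cohorts are compared on the observation scores one variable at a time. For the choice of test the section has: "using independent sample *t* tests and Mann-Whitney *U* testing, as appropriate". The scores are thus treated as continuous or ordinal, and nothing is adjusted for.
- **Multivariable modelling.** "A variable-selection strategy will be used to create multivariate models". The next sentence names the only model type: "Binary logistic regression will be conducted to calculate odds ratios and 95% confidence intervals for significant predictors on univariate analysis and clinically relevant covariates". It does not say what the dependent variable is.

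Under Primary outcome measurements, "Nontechnical skills will be observed using five different methods": four rating tools (NOTSS, Oxford NOTECHS II, OTAS, ICARS) and human factor analysis. Perioperative events are listed there too. Data collection and handling adds that the software allows the duration of behaviours and events to be measured. No threshold is given for any of these.

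The Design section describes a "prospective, observational, multicentre, nonrandomised, case-control study". On allocation, Inclusion criteria states: "The choice of treatment is at the discretion of the patient and the surgeon". Patient characteristics that could serve for adjustment are recorded under Secondary outcome measurements, beginning with "Age, World Health Organization performance status, Charlson comorbidity index, neoadjuvant chemotherapy, prior local treatment, prior radiation therapy in the surgical field".

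**The concern.** The hypotheses ask how the robot-assisted approach changes nontechnical skills. Because approach is not randomised, case difficulty could differ between cohorts, and difficulty could itself affect how a team behaves. An adjusted comparison of the scores is therefore the natural main analysis.

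The text gives an unadjusted test of the scores and then a regression family meant for a different type of outcome. Followed as published, the plan would judge the hypotheses about the scores on tests that cannot separate approach from case mix. The odds ratios reported beside them would answer some other question, and the article does not say which.

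**Working it through.** **1. What could the logistic model have as its dependent variable?** The article leaves three readings open.

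- *A binary patient outcome*, such as a complication or a positive surgical margin. This is an ordinary use and fits the aim of studying surgical outcomes. It gives no adjusted effect of approach on the scores.
- *Open versus robot-assisted, predicted from the scores.* This gives the odds of having had one approach per unit of score. Exposure and outcome are reversed, so it is not an effect of approach on skills.
- *A score cut in two.* This would give an adjusted odds ratio for approach, but no cut-point is planned. Dichotomising also costs power. With an assumed true difference of 0.5 SD, a score kept whole has about 48% power at 29 per group and 96% at 112. Split at the midpoint between the group means, it has about 32% and 85%.

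No reading gives an adjusted effect on the scores' own scale.

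**2. Group sizes.** These come from Time scales and Centre details; the article states no sample size to reproduce. Inclusion runs from January 2021 to August 2022, about 20 months.

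- Eindhoven: 35 per year × 20/12 = 58.3, half expected to be robot-assisted, so about 29 per approach.
- Amsterdam: 50 per year per approach × 20/12 = 83.3.
- Both centres: 29.2 + 83.3 = 112.5, so about 112 per approach.

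These are upper figures, since they assume every procedure is included although patients and staff must consent.

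**3. False rejection by the unadjusted test.** Assume no true effect of approach. Let one case-mix variable correlate r with the score and differ by δ SD between cohorts; r and δ are assumptions, because the article gives neither.

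- Bias in the score difference = r × δ, in SD units of the score.
- Standard error of the difference = √(2/n): √(2/112) = 0.134 and √(2/29) = 0.263.
- With z = rδ / √(2/n), rejection probability = Φ(z − 1.96) + Φ(−z − 1.96).

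| n per group | r | δ | bias | z | rejection |
|---|---|---|---|---|---|
| 112 | 0.4 | 0.3 | 0.12 | 0.90 | 15% |
| 112 | 0.4 | 0.5 | 0.20 | 1.50 | 32% |
| 112 | 0.2 | 0.3 | 0.06 | 0.45 | 7% |
| 112 | 0.2 | 0.5 | 0.10 | 0.75 | 12% |
| 29 | 0.4 | 0.3 | 0.12 | 0.46 | 7% |
| 29 | 0.4 | 0.5 | 0.20 | 0.76 | 12% |
| 29 | 0.2 | 0.3 | 0.06 | 0.23 | 6% |
| 29 | 0.2 | 0.5 | 0.10 | 0.38 | 7% |

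A simulation with 1,500 replicates at 112 per group and r = 0.4 agrees: 14% and 31% unadjusted, against 4% and 5% with the covariate in the model.

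**The case against.** The strongest reply is that this is a condensed article. The sentence on multivariate models is generic, and an analysis plan not shown may name each dependent variable and further model types. That stands as a limit: one cannot say that no adjusted effect will ever be estimated, only that the published plan specifies none. It does not remove the point, because the article itself names one model family, and that family does not match the scores which the same paragraph tests as continuous or ordinal.

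A reader might infer more than the text supports in these respects:

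- *That confounders without univariate significance will be dropped.* The sentence also admits clinically relevant covariates, so selection is not by screening alone. What can be said is that univariate significance is one route into the model and that no covariates are named.
- *That the model must predict approach from scores, as the case-control label hints.* The label is weak evidence, and a binary patient outcome is at least as likely.
- *That no primary outcome is binary.* Occurrences of behaviours are registered, and human factor findings could be coded present or absent. The mismatch is with ratings, counts and durations.
- *That scores will be split at the median, at a calculable cost in surgeries.* No split is planned, so the power loss above applies only if one were adopted.
- *That case complexity does differ between cohorts.* Discretionary choice makes this possible but does not establish it.
- *That listing patient characteristics under secondary outcomes bars adjustment for them.* This is a matter of labelling; they are recorded and can be used.

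It is also fair to say that patient covariates cannot isolate approach in Eindhoven. There, under Study population, one surgeon performs all open procedures and another all robot-assisted ones. That stands, and belongs in the limitations.

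**Conclusion.** The concern holds for the published plan. Approach is compared on the primary scores by unadjusted tests only, and the single regression family named does not suit ratings, counts or durations. No adjusted effect of approach on those scores is specified unless a score is dichotomised, for which no cut-point is given.

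The size depends on assumptions outside the document. For an imbalance of 0.3 to 0.5 SD, a nominal 5% test rejects falsely about 15% to 32% of the time at 112 per group with a correlation of 0.4, and about 7% to 12% with a correlation of 0.2. At 29 per group, the size of the within-Eindhoven comparison, the figures are about 7% to 12% at correlation 0.4 and close to nominal at 0.2. So the problem is material for the pooled comparison if a moderately prognostic case-mix variable is imbalanced, and smaller within Eindhoven. The calculation treats procedures as independent and considers a single confounder.

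**What to change.** - State the dependent variable of every model.
- For the approach comparison, make each nontechnical skills score the dependent variable in a linear or ordinal model, with count or duration models where the measure calls for them. Enter approach, or case number for the learning curve, as the exposure.
- Fix the adjustment set in advance from variables already recorded: age, performance status, Charlson index, prior abdominal or pelvic surgery, prior radiation in the surgical field and neoadjuvant chemotherapy. Let this replace selection by univariate significance.
- Keep logistic regression for binary patient outcomes such as complications or surgical margins.
- State as a limitation that approach and surgeon cannot be separated within Eindhoven.

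The cost is a revision of the statistics text and a little more analysis work. No new data are needed.
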